**Sponsor's Protocol # *IRB00000594***

### **Research Question:**

This study is a randomized controlled trial among HIV-positive injecting drug users (IDUs) to reduce high risk injecting and sexual behaviors in Thai Nguyen, Vietnam. We will be conducting this study in collaboration with the Thai Nguyen Centre for Preventive Medicine (CPM). We will compare standard HIV voluntary counseling and testing (VCT) to an intervention that adds a continuum of psychosocial support for HIV-positive IDUs. Our intervention includes community-based stigma reduction programs, and will assess both individual and structural interventions. Our research questions for the overall project are:

1. What is the impact of perceived HIV-related stigma on disclosure, social support and coping among IDUs?
2. What roles do disclosure, social support and coping play in facilitating the reduction of HIV-risk behaviors
3. Are combined individual and structural level interventions more effective in reducing injecting and sexual behaviors among HIV-positive IDUs than individual and structural interventions alone and more effective than the standard HIV VCT?

### *Hypothesis*

Our primary hypothesis is that the combined individual and structural level activities is effective in reducing injecting and sexual behaviors. Our secondary hypothesis is that network members of IDUs assigned the individual and structural level interventions will have decreased HIV incidence after 24 months.

### **Rationale:**

#### *Background*

HIV-positive IDUs occupy a critical place among HIV-positive risk groups because they can potentially transmit the HIV virus through two routes: unprotected sex and unsafe drug use (1). In Vietnam, IDUs account for over 65% of all reported HIV infections, and HIV sentinel surveillance indicates that HIV continues to increase in all surveillance groups, including IDUs (2). With rising HIV prevalence, increasing IDUs and female sex worker population who use drugs, IDUs may soon influence HIV risk in the general population. Interventions that enhance HIV knowledge, facilitate voluntary disclosure of HIV status and strengthen social support among HIV-positive persons may reduce sexual and injecting risk behaviors, which in turn, reduce HIV transmission (3-6).

HIV-related stigma has been widely reported in Vietnam, and is one of the main obstacles to prevention, care and treatment of HIV/AIDS (7-9). People living with HIV (PLWH) in Vietnam

often experience severe social marginalization within families, communities, schools and in the workplace, discrimination in health care settings, and internalized stigma (7, 10). As a result, stigma prevents disclosure of HIV status to others and is a profound barrier to HIV prevention, access and support in Vietnam.

### *Aims*

The specific aims of this project are:

1. To qualitatively explore the impact of perceived HIV-related stigma on disclosure, social support and coping among IDUs, and to explore, in turn, the role of disclosure, social support and coping in facilitating the reduction of HIV risk behaviors among HIV-positive IDUs in Thai Nguyen, Vietnam.
2. To conduct a four-arm randomized attention-controlled intervention trial among HIV-positive IDUs. The four arms of the trial are: 1) an attention-controlled condition; 2) individual-level posttest counseling and skill-building support groups; 3) structural-level stigma reduction programs; and 4) both individual and structural level activities.

### **Methods:**

#### *Study Design and Rationale:*

##### **Phase I: Formative:**

Formative ethnographic research will be used to explore the impact of perceived HIV-related stigma on disclosure, social support, and coping among IDUs and to explore the role of disclosure, social support, and coping in facilitating the reduction of HIV risk behaviors among HIV-positive IDU to help inform the intervention and refine measures used in the survey instrument. To achieve this, we will conduct qualitative interviews with the following goals:

- 1.) Explore the impact of HIV-related stigma on disclosure, social support and coping and to explore the role of stigma, social support and coping in facilitating the reduction of HIV risk behaviors among HIV-positive IDUs
- 2.) Describe women's experiences with their partner's HIV-serostatus disclosure
- 3.) Describe community attitudes and behaviors towards HIV-positive individuals and towards the Women's Union and Youth Union
- 4.) Conduct a pilot of assessment measures
- 5.) Conduct a pilot of components of the intervention.

##### **Phase II-IV: Baseline, Intervention and Evaluation**

To determine the effects of combined and separate individual and structural level activities on injecting and sexual behaviors, a four arm randomized intervention trial will be conducted. Two villages will be randomly selected from each of the 4 districts in Thai Nguyen with the largest numbers of IDUs. Within each district, one village will be randomly assigned to receive the stigma reduction programs and the other to receive the control, and within each village (regardless of stigma reduction assignment) a random half of the Index IDUs will be assigned to the intervention (enhanced posttest counseling and skill building support groups) and the other half to the control. The overall study design is shown below in Figure 1. The primary outcomes among

Index participants will be drug-related and sexual risk behaviors. The primary outcome among Network participants will be HIV incidence. The intermediate outcomes will include perceived stigma, correct condom use, partner uptake of HIV VCT, perceived social support, depression, and self-reported disclosure.

**Figure 1. Study Design**

[figure not shown]

Among participants who are randomized to the intervention arm and who return for their follow-up assessments, we will conduct qualitative interviews among 10 participants at each follow-up visit. The purpose is to explore participants' experiences with injecting and sexual behavior changes and HIV-related stigma.

To assess operational outcomes across study arms, we will compare participants' perceived quality of sessions, proportion of IDUs attending all posttest counseling sessions and cost of service provision and opportunity cost incurred by participants. We will use ongoing in-depth interviews with a subset of our participants, analysis of project records, including participant evaluation forms, counseling and session log forms and financial records. Outcome evaluation will include pre-intervention assessment of participants with post-intervention follow-ups at 3, 6, 12, 18 and 24 months.

To assess HIV incidence among HIV-negative injecting network members of HIV-positive IDUs, injecting partners of HIV-positive IDUs enrolled in the intervention trial will be screened and tested for HIV status and a follow-up assessment will be conducted 24 months from the intervention start date of their respective index IDUs. Network members will be asked to provide a list of names of their injecting partners and their injecting practices with each partner over the past two years, enabling assessment of the possibility of network member's HIV exposure through injecting sources other than through the index participant.

## **Population:**

### **Phase I: Formative**

#### *Sample Size:*

Approximately 170 participants will be recruited for ethnographic interviews, including in-depth interviewees and focus group discussants. We will conduct 24 in-depth interviews with male HIV-positive IDUs and 10 in-depth interviews with female partners of IDUs in order to explore the impact of HIV-related stigma on disclosure, social support and coping and the roles of disclosure, social support and coping in facilitating the reduction of HIV risk behaviors, and to explore women's experiences with their partner's HIV-serostatus disclosure. We will also do two additional in-depth interviews with men of unknown HIV status and unknown drug using status so as to avoid the possibility of the HIV-positive IDUs from being identified as such. Similarly we will interview 2 additional women of unknown partnership, HIV or IDU status for the same reason. We will conduct 2 focus group discussions among 8 men of unknown HIV and drug using status, 2 focus group discussions among 8 women of unknown HIV and drug using status, and 1 focus group discussion among community leaders to understand HIV-related stigma and to assess community attitudes towards the Women's and Youth Unions. We will also conduct 4 focus group discussions of 6-8 men and women in the community to pilot components of the community-level intervention, 6 focus group discussions among 6-8 male HIV-positive IDUs to pilot components of the individual-level intervention. In addition, we will pilot assessment measures among 20 HIV-positive male IDUs.

#### *Power Calculations or Statistical Plan:*

Because qualitative research stresses depth more than breadth and insight more than generalization, sample sizes are relatively small compared to survey research. The sample size depends on the number of people needed to adequately answer the research question.

#### *Inclusion and Exclusion Criteria:*

Individuals to be selected for all qualitative interviews will: 1) be 18 years of age or older; 2) reside in Thai Nguyen province and 3) be capable of providing voluntary informed consent. Individuals will be excluded if they 1) are younger than 18 years of age; 2) reside in communities outside of Thai Nguyen province; or 3) are incapable of providing voluntary informed consent.

Individuals selected for in-depth interviews on the impact of HIV-related stigma also will 1.) be male; 2.) be an HIV-positive current or former injection drug user who was screened in our former study but was not enrolled due to their HIV seropositive status; 3) have indicated willingness to be contacted for future study; 4) have known his HIV status for approximately 1 year.

Individuals selected for in-depth interviews on women's experiences with their partners HIV-serostatus disclosure also will 1) be female; and 2) be a sexual partner of an HIV-positive IDU.

Individuals selected for piloting assessment measures or for piloting individual-level intervention components also will: 1.) be HIV-positive injection drug users.

#### *Gender, Age and Locale*

Based on our HIV-negative study, the vast majority of IDUs in Thai Nguyen are male (97%), are heterosexual (none reported sex with another man) and in their mid-to-late twenties. We've restricted participation to those 18 years and older because under Vietnamese regulations, individuals 18 years and older can independently consent to participate in a research study without the consent of a parent.

In-depth interviews and focus group discussions will be conducted at a private assessment venue located centrally in Thai Nguyen province.

#### **Phase II-IV: Baseline, Intervention and Evaluation**

#### *Sample Size and Power Calculations*

For our primary hypothesis, that Index IDUs assigned the individual and structural level interventions will have decreased frequency of sexual and injecting risk behaviors, a total sample size of 404 HIV-positive IDUs enables us to detect a 40% or 50% decrease in sexual and injection risks, accounting for a 20% drop-out rate. Power calculations assumed intention-to-treat distributions, 85% power and an alpha of .05. With a sample size of 404, we can detect decrease in frequency of unprotected sex of .40 or above (assuming the stigma reduction programs are as effective as the individual-level intervention; .50 or above if it's 50% as effective) for analyses on IDUs. If the variance covariance parameters are similar between the sexual and drug risk trajectories, we can also detect an increase in frequency of using new needles and syringes of .40 or above for analyses on IDUs.

For our secondary hypothesis, that network members of IDUs assigned the individual and structural level interventions will have decreased HIV incidence, we estimate that a sample size of 400 (200 combined sample size for the arm receiving both interventions and the arm receiving both controls) HIV-negative network members will enable us to assess differences in HIV incidence among the HIV-negative injecting network members of HIV-positive IDUs, accounting for a 20% drop-out rate ( $160 \times 2 / (1 - 20/100)$ ). With 80% power and alpha of .05, we can detect a decrease in 24-month HIV incidence of between 20 -25% or more for analyses on injecting network members.

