### **Safety Monitoring:**

Safety monitoring will be performed by an independent Data Safety Monitoring Committee comprised of researchers from Hanoi and individuals in Thai Nguyen with expertise in issues relevant to this study.

The committee will meet initially to review the protocol prior to submission to the Thai Nguyen Centre for Preventive Medicine IRB and before data collection begins, after which it will convene to review the study within one year of commencing enrollment and at least annually thereafter. Emergency meetings of the committee will be convened as needed.

At each meeting review of interim reports, the DSM Committee will review the following in a report prepared by a statistician external to the study team:

- Expected versus actual accrual rates
- Study retention rates, total and by study arm (unblinded)
- Study outcomes, as available, total and by study arm (unblinded)
- Numbers of adverse events and serious adverse events, by type, total and by study arms (unblinded)
- Any quality assurance or regulatory issues that occurred since the previous review
- Any actions or changes with respect to the study protocol.

Blind interim analyses of the data will be conducted halfway through the follow-up period, where virtually all participants will have provided 6-month behavioral interim endpoints. Interim reports will be prepared for the DSM Committee by an external statistician and will be presented to the protocol team blinded as to study arm, labeled as "A", "B", "C" "D".

Consideration will be given to stopping the study under each of the following scenarios.

- Increases in the overall number of drug use and risk behaviors for all study participants, as compared to baseline levels, that are statistically significant at the  $p < 0.001$  level.
- Differences in study outcomes between the control arm (receiving neither intervention) and any of the three study arms that are statistically significant at the  $p < 0.001$  level.

- Differences in the number of serious adverse events (calculated by collapsing all SAEs) between the control arm (receiving neither intervention) and any of the three study arms that are statistically significant at the  $p < 0.001$  level. SAEs include mortality, suicide, accidents and violence.

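### The 85% power shows no allowance for randomising the stigma programme by eight villages, and is unsupported for the combined-versus-neither contrast unless between-village variance is near zero or already counted

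*Protocol*

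**What the plan says.** The design section for Phases II-IV (Baseline, Intervention and Evaluation) takes two villages from each of four districts. Within a district, "one village will be randomly assigned to receive the stigma reduction programs and the other to receive the control". Inside every village, half of the index participants are then randomised to the individual-level intervention.

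The Hypothesis section puts the primary hypothesis on the combined intervention. Sample Size and Power Calculations sizes that hypothesis: "a total sample size of 404 HIV-positive IDUs enables us to detect a 40% or 50% decrease in sexual and injection risks". One-fifth attrition is the only inflation that it mentions for this number. It adds: "Power calculations assumed intention-to-treat distributions, 85% power and an alpha of .05". The effect is described as "we can detect decrease in frequency of unprotected sex of .40 or above". That value holds if the structural programme works as well as the individual one; if it works half as well, the detectable effect becomes .50. The only reference to variance is conditional: "If the variance covariance parameters are similar between the sexual and drug risk trajectories". No values are given, and the section names no village, ICC, design effect or village-based degrees of freedom.

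Safety Monitoring lists, among the grounds for considering stopping, "Differences in study outcomes between the control arm (receiving neither intervention) and any of the three study arms that are statistically significant", with the threshold set at p < 0.001.

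**The concern.** The combined arm exists only in the four stigma-programme villages and the double-control arm only in the other four. Any stable difference between the two sets of villages therefore goes straight into the combined-versus-neither contrast, and recruiting more men per village does not remove it. A power figure that shows only a drop-out allowance is a figure for independently randomised participants.

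Two misreadings are at stake. A null result could be taken as a well-powered negative. A positive result from a participant-level test could be a difference between villages. The individual-level contrast is compared within villages and does not share the problem.

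**Working it through.** **Inputs from the protocol.** 404 enrolled, 20% drop-out, 85% power, alpha .05 (taken as two-sided; the protocol does not say), 8 villages, 2 arms per village.

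**Inputs assumed.** Equal enrolment per village and arm; ICC of .01, .02 or .05.

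**The plan's own figure.** The total is consistent with 323 / 0.8 = 403.75, rounded up to 404. The 85% cannot be reproduced, because no standard deviation, baseline rate, within-person correlation or test is given. As an illustration, read .40 as a standardised difference: 2 × 2.996² / 0.40² = 112.2, so 113 per arm, and 4 × 113 / 0.8 = 565 in total. With 81 evaluable per arm, power would be 72% at .40 and 89% at .50. This does not show the 85% to be wrong, since the scale is unknown. I therefore grant exactly 85% under independence and ask what village randomisation does to it.

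**Cell size.** 404 × 0.8 / 16 village-by-arm cells = 20.2 men.

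**Design effect.** The contrast compares four cells in four villages with four cells in four other villages, so DE = 1 + (20.2 − 1) × ICC:
- ICC .01: 1 + 19.2 × .01 = 1.19
- ICC .02: 1.38
- ICC .05: 1.96

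**Ceiling with a normal reference.** The non-centrality that gives 85% is 1.960 + 1.036 = 2.996. Power = Φ(2.996/√DE − 1.960):
- ICC .01: 2.744 − 1.960 = 0.784, so 78%
- ICC .02: 2.547 − 1.960 = 0.587, so 72%
- ICC .05: 2.140 − 1.960 = 0.180, so 57%

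**Small-sample reference.** The design is a split plot. Combined minus neither equals the structural effect (between villages) plus the individual effect (within villages). In units where the total variance is DE, the between-village stratum contributes 20.2 × ICC + (1 − ICC)/2 and the within-village stratum (1 − ICC)/2. The between stratum has 6 degrees of freedom (unpaired villages) or 3 (district pairs). The within stratum has about 16 × 19 = 304. Satterthwaite's formula combines them.
- ICC 0: the shares are .5 and .5. Unpaired df = 1/(.5²/6 + .5²/304) = 23.5; paired df = 11.9.
- ICC .02: the between share is (.404 + .490)/1.384 = .646. Unpaired df = 1/(.646²/6 + .354²/304) = 14.3. The non-central t with non-centrality 2.547 gives 66%.

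Simulation with 20 men per cell, estimating both variances in each run, gives the last two columns:

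| ICC | Normal reference | Split plot, unpaired | Split plot, district-paired |
|---|---|---|---|
| 0 | 85% | 82% | 77% |
| .01 | 78% | 73% | 68% |
| .02 | 72% | 66% | 60% |
| .05 | 57% | 50% | 44% |

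Rejection under the null was about 5% unpaired and roughly 5.5 to 6.5% paired. The paired column assumes that district matching removes no variance.

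**Type I error if men were treated as independent.** 2 × [1 − Φ(1.960/√DE)] gives 7%, 10% and 16% at the three ICCs. For a nominal .001 criterion, 2 × [1 − Φ(3.29/√DE)] gives about .003, .005 and .019. This affects two of the three monitoring contrasts with the control arm (structural alone and combined), because only individual-alone versus control is within village.

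**The case against.** The strongest reply is that the omission is inferred from silence. The section mentions variance-covariance parameters for risk trajectories, so some longitudinal model lay behind the figure, and a village component cannot be strictly excluded. The ICC is wholly assumed, and gains from baseline adjustment, five follow-ups or effective district matching are not modelled. All of this stands. It limits the claim to what the section shows and supports, and makes the size conditional.

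A reader might go further in three ways.
- **Much lower power.** Collapsing to village-cell means and using a t-test gives 63/57/44% (6 df) or 47/42/32% (3 df) at the three ICCs, and 71% or 53% even at ICC 0. Those figures describe a test that discards the within-village information on the individual component. The design supports a better one.
- **A floor on the p-value.** With four pairs there are 2⁴ = 16 structural assignments, so an exact test that re-randomises only these cannot give a two-sided p below 2/16 = 0.125. That does not bind the combined contrast: under the null that neither intervention works, the within-village allocations are re-randomised too.
- **An inflated error rate in this trial.** Nothing in the protocol says participants will be analysed as independent, so the type I error figures are conditional. The monitoring criterion also prompts consideration of stopping, weighed with overall risks and benefits; it is not a binding rule.

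The choice of test may properly be left to an analysis plan that is not shown. The 85% is stated in the protocol itself, and no choice of test adds villages.

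**Conclusion.** The concern holds in limited form. The protocol's 85% shows no allowance for assigning the structural programme to four villages against four. For the combined-versus-neither contrast it is unsupported unless between-village variance is essentially zero or is already in the unprinted inputs. If 85% is the power under independence, every positive ICC takes it below 85%. At ICCs of .01/.02/.05 it is at most about 78/72/57%, and about 73/66/50% or 68/60/44% once the few villages are reflected in the degrees of freedom. At the low end the loss is moderate: at .01 it runs from 7 to 17 points.

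These figures rest on the assumed ICCs, equal enrolment per village and a two-sided test. The protocol does not spell out the primary comparator. Combined versus neither is the natural reading, since the third research question sets the combination against standard testing and counselling. Combined versus individual alone would also be between villages; combined versus structural alone would not.

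It would go too far to say that the sponsor ignored clustering, that the design has been shown to miss its power target, or that the arithmetic is wrong. The documents do not disclose enough for any of these.

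**What to change.** 1. In Sample Size and Power Calculations, replace the single 85% for the combined contrast with power over a stated ICC range. Compute it from a model with a village random effect, district as stratum and small-sample degrees of freedom. If the existing calculation already has a village component, print it.
2. Give a separate power figure for the individual-level contrast, which is randomised within villages.
3. State that structural and combined contrasts use this village-respecting model at the final analysis and for the p < 0.001 monitoring criterion. Do not require a test on village pairs alone for the combined contrast, because that discards the within-village information.

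The cost is a recalculation and some protocol wording. No extra participants or villages are needed to make the statement accurate, and no clinical procedure changes. The price is a less favourable stated power for the primary hypothesis.
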